### 3.3.2 Sintilimab Injection

Administer according to the administration method and dosage in the Sintilimab instructions, 200 mg, intravenous infusion, Q3W.

### 3.3.3 Hepatic Arterial Infusion Chemotherapy (HAIC)

Based on the clinical routine experience of this research center, the FOLFOX regimen was selected for HAIC, with the following doses: Oxaliplatin 85 mg/m^2^ infusion for 2 hours, Leucovorin 400 mg/m^2^ infusion for 2 hours, 5-FU 400 mg/m^2^ bolus for 10 minutes, followed by continuous infusion of 5-FU 1200 mg/m^2^ for 23 hours. The first HAIC will be implemented on the date predetermined by the investigator, followed by once every 3 weeks (Q3W). The total number of HAIC treatments will be determined by the investigator based on the actual condition of the patient as needed.

## 3.4 DLT Assessment and Judgment Criteria

DLT is defined as any of the following adverse events, unless the investigator determines that it is definitely related to the study progression or caused by other external factors, it will be considered as DLT:

Hematologic Toxicity:

- - - 1. Grade 4 neutropenia lasting more than 7 days.
      2. Febrile neutropenia [defined as an absolute neutrophil count (ANC) < 1×10^9^ /L, accompanied by a single temperature reaching 38.3℃ or a temperature of 38℃ persisting for more than one hour].
      3. Grade 3 neutropenia with infection.
      4. Grade 3 thrombocytopenia with severe uncontrollable bleeding events.
      5. Grade 4 thrombocytopenia.
      6. Grade 4 anemia (life-threatening).
      7. Grade 3 or 4 lymphopenia with opportunistic infections.

Non-hematologic toxicity:

Skin reactions: severe hand-foot skin reaction (HFSR) or other skin adverse reactions that persist for >2 weeks or occur a second time despite appropriate intervention.

Blood pressure: persistent/recurrent systolic blood pressure ≥160 mmHg or diastolic pressure ≥100 mmHg on the second occurrence, and remains uncontrolled despite aggressive antihypertensive treatment. (Persistent/recurrent blood pressure ≥160/100 mmHg refers to measurements of ≥160/100 mmHg taken at least twice with an interval of 24 hours, with each measurement taken after the subject has been seated and resting quietly for more than 5 minutes.) At least 1 week of antihypertensive medication is allowed before the second recorded hypertension event occurs.

Cardiac contractile function: First occurrence of LVEF decrease >10%, or LVEF value <40%.

Gastrointestinal system: Grade 4 diarrhea, or Grade 3 diarrhea lasting >24 hours despite active antidiarrheal treatment, or occurrence of two episodes of Grade 3 diarrhea regardless of duration; Occurrence of ≥ grade 3 nausea and vomiting despite adequate/maximum medical intervention and/or preventive measures.

Absolute QTcB ≥500 msec (at two consecutive time points).

Other Grade 4 or higher adverse events.

Grade 3 or higher immune-related adverse events (irAE).

Other Grade 3 toxic effects, except for laboratory abnormalities that recover to Grade 2 (inclusive) or below within 3 days (asymptomatic and not requiring medical intervention).

In addition to the above events, DLT events also include any level of toxic reaction that the investigator considers necessitating the subject's withdrawal from the study.

# Study Population

## Inclusion criteria

Patients who meet all of the following criteria may be included in this study:

1. Voluntary enrollment with signed written informed consent;
2. Aged 18 to 80 years (inclusive), regardless of gender;
3. Patients with hepatocellular carcinoma clinically diagnosed according to the 'Guidelines for the Diagnosis and Treatment of Primary Liver Cancer (2019 Edition)' or confirmed by histological/cytological diagnosis;
4. Patients with unresectable or metastatic hepatocellular carcinoma;
5. No prior systemic treatment. Patients who have received adjuvant chemotherapy after local treatment may also be included if the chemotherapy ended more than 12 months ago and there has been disease progression or metastasis;
6. The last intervention, radiotherapy, and ablation treatment must have ended more than 4 weeks ago;
7. Patients who have previously undergone liver resection should have R0 resection, and tumor recurrence should occur more than 24 months after surgery;
8. There must be at least one assessable lesion (according to RECIST 1.1 criteria) ;
9. Expected survival time ≥ 3 months;
10. Eastern Cooperative Oncology Group (ECOG) performance status (PS) score of 0-1;
11. Child-Pugh score ≤ 7;
12. Able to cooperate in observing adverse events and efficacy;
13. Major organ functions are normal, meeting the following criteria:

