| **Research Process** | **Screening Period:**  The investigator must fully inform the patient of the potential benefits and risks of this clinical trial. After the patient voluntarily signs the informed consent form, various screening examinations will begin, including the following items:  1) Collect medical history, smoking history, alcohol history, and demographic data  2) Vital signs, physical examination, blood pressure monitoring, ECOG score  3) Adverse events, concomitant medication  4) Laboratory tests   - Complete blood count: including red blood cell count, hemoglobin, hematocrit, white blood cell count and differential (neutrophils, lymphocytes, eosinophils, monocytes, basophils) and platelet count; - Blood biochemistry: including total protein, albumin, globulin, blood glucose, urea/urea nitrogen, creatinine, alkaline phosphatase, lactate dehydrogenase, total bilirubin, direct bilirubin, indirect bilirubin, AST, ALT, γ-glutamyl transferase, calcium, phosphorus, magnesium, potassium, sodium, chloride, amylase, uric acid, creatine kinase, troponin; - Virology tests: Hepatitis B qualitative five items and HBV-DNA, HCV-RNA, HIV; - Tumor markers: AFP; - Thyroid function: TSH, free T3, free T4; - Urinalysis: including specific gravity, pH, urine glucose, protein, casts, ketones, urine red blood cells, urine white blood cells; If there are two consecutive urine protein tests showing ++ or higher, or if the doctor determines the results to be abnormal and clinically significant, a 24-hour urine protein quantification test is required; - Fecal occult blood; - Coagulation function: TT, PT, INR, APTT; - Cardiac ultrasound examination: particularly pay attention to the evaluation of left ventricular ejection function; - 12-lead electrocardiogram (ECG); - Imaging examination: CT or MRI (Note: examinations conducted within 4 weeks prior to screening at the same institution are acceptable); - Women of childbearing age must undergo pregnancy testing to exclude pregnancy;   If all the above screening examination items meet the enrollment criteria for this study, the patient will be enrolled.  **Treatment period:**  After enrollment, subjects will first take oral donafenib tablets for 3 to 7 days. After the investigator assesses that the subjects can tolerate it, the subjects will receive intravenous infusion treatment with sintilimab injection. On the day of sintilimab infusion or the following day, they will begin approximately 1 day of HAIC treatment (the total number of subsequent HAIC treatments will be conducted as needed by the investigator based on the patient's actual condition). Afterwards, subjects will visit every 3 weeks (calculated from the day of the first infusion of sintilimab), with a time window of ±3 days. Every 6 weeks, imaging assessments will evaluate efficacy (using both RECIST v1.1 and mRECIST criteria for tumor assessment), until the subject first shows imaging-confirmed disease progression (meeting both RECIST v1.1 and mRECIST criteria for imaging progression) or intolerable toxicity.  **Follow-up after treatment ends:**  Patients need to undergo safety follow-up and survival follow-up after treatment ends.  In addition, for patients who have not progressed but discontinued treatment due to intolerance, follow-up is required every 12 weeks (within 2 years after the first administration) or every 24 weeks (after 2 years of the first administration) until definitive imaging evidence of progression or death is obtained.  For specific follow-up times and related examination items, please refer to the flowchart. |

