2. CT/MRI examinations, with sites including the chest and abdomen; if clinical indications or suspicion of metastasis arise in other areas, CT/MRI examinations will be conducted; Chest imaging examinations should primarily use CT scans, while abdominal imaging examinations should primarily use enhanced MRI; if the subject is allergic to CT contrast agents, has poor renal function, or has other reasons that make CT examinations unsuitable, MRI will be used instead of CT; For CT/MRI examinations conducted as part of routine diagnosis prior to the subject signing the ICF, if they were performed within 4 weeks before enrollment and at this research center, they do not need to be repeated;
3. Review inclusion and exclusion criteria, and assess the eligibility of subjects for inclusion;
4. Record adverse events: Adverse events occurring from the signing of the informed consent form (ICF) until the first administration of the treatment should be recorded on the medical history page of the case report form (CRF);
5. Record concomitant medication/treatment: All medications/treatments received by subjects must be recorded in the CRF starting from 28 days prior to enrollment, including the generic name of the drug, dosage, frequency, route of administration, the reason for using the drug/treatment, and the start and end dates. Any new changes in drug treatment must be continuously updated.

Patients may retest laboratory parameters that do not meet the inclusion criteria within the screening window. Laboratory assessments are conducted as part of the screening evaluation and do not need to be repeated prior to medication administration.

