**3.1.3 Special Considerations for Measurable Lesions**
Special attention is required for bone lesions, cystic lesions, and lesions that have previously undergone local treatment:
Bone Lesions:

- Bone scans, PET scans, or plain films are considered inadequate imaging techniques for measuring bone lesions. However, pharmacologically, these techniques can be used to confirm the presence or absence of bone lesions.
- If the soft tissue component meets the aforementioned criteria for measurability, osteolytic lesions with identifiable soft tissue or mixed acute osteolytic lesions can be assessed using cross-sectional imaging techniques such as CT or MRI, and they may be considered measurable lesions.
- Osteolytic lesions are unmeasurable.

Cystic lesions:

- Simple cysts defined by X-ray that meet the inclusion criteria should not be considered malignant lesions (neither measurable nor unmeasurable), as by definition, they are simple cysts.
- If the definition of measurable lesions is met, cystic lesions presenting as cystic metastases may be considered measurable lesions. However, if there are non-cystic lesions present in the same patient, priority should be given to the target lesions.

Lesions previously treated locally:

- Tumor lesions located in previously irradiated areas or those subjected to other local treatments are generally not considered measurable unless it has been demonstrated that the lesions are still ongoing. The research protocol should specify under what conditions such lesions will be considered measurable.

**3.2 Measurement Method Specifications

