**4. Tumor Efficacy Assessment**

**4.1 Assessment of All Tumors and Measurable Lesions**

To evaluate objective response or potential future progression, it is necessary to conduct a baseline assessment of the total tumor burden for all tumor lesions, serving as a reference for subsequent measurement results. In clinical protocols where objective response is the primary treatment endpoint, only patients with measurable lesions at baseline are eligible for inclusion. Measurable lesions are defined as the presence of at least one measurable lesion. For trials where disease progression (time to progression or degree of progression at a fixed date) is the primary treatment endpoint, the inclusion criteria must clearly specify whether it is limited to patients with measurable lesions or if patients without measurable lesions can also be included.

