**4.3.1 Efficacy Evaluation of Target Lesions**

Complete Response (CR): All target lesions disappear, and the short axis value of any pathological lymph nodes (regardless of whether they are target lesions) must be < 10 mm.

Partial Response (PR): A decrease of at least 30% in the sum of the diameters of all target lesions, relative to the baseline total diameter.

Disease Progression: An increase of at least 20% in the sum of the diameters of all target lesions, using the minimum diameter of lesions as a reference (including the baseline total diameter of lesions, if it is the minimum value). Additionally, in addition to the relative increase of 20% in the sum of diameters, the absolute value of the sum must also increase by at least 5 mm (Note: The appearance of one or more new lesions can also be considered disease progression).

Stable Disease (SD): Using the sum of the minimum diameters of lesions during the study as a reference, lesions that shrink do not meet the criteria for PR, and lesions that increase do not meet the criteria for disease progression.

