**Table 2 Time Point Response - Subjects with Non-Target Lesions Only**

| **Non-Target Lesion** | **New Lesion** | **Overall Response** |
| --- | --- | --- |
| CR | Non | CR |
| Non-CR or non-disease progression | Non | Non-CR or Non-Disease Progression |
| Not Fully Assessable | Non | Not Assessable |
| Unclear Disease Progression | Yes or No | Disease Progression |
| Any Situation | Yes | Disease Progression |

Note: For non-target lesions, 'Non-CR/Non-Disease Progression' refers to efficacy better than SD. As SD is increasingly used as an endpoint for evaluating efficacy, the efficacy of Non-CR/Non-Disease Progression has been established to address situations where no measurable lesions are defined.

For unclear progression findings (such as very small uncertain new lesions; Treatment for cystic changes or necrotic lesions of the existing lesions can continue until the next evaluation. If disease progression is confirmed at the next evaluation, the date of progression should be the date when suspected progression first occurred.

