3.2 Measurement Method Description

3.2.1 Lesion Measurement

All tumor measurements in clinical evaluations must be recorded in metric units. All baseline assessments of tumor lesion size should be completed as close to the start of treatment as possible, and must be completed within 28 days (4 weeks) prior to the start of treatment.

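### Inclusion item 8 asks for an assessable rather than a measurable lesion although ORR is primary, so patients who could respond only by CR may enter the denominator; the baseline-scan windows also disagree

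*Protocol*

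**What the plan says.** **Eligibility.** Item 8 has the same wording in the Protocol Summary and Section 4.1: "There must be at least one assessable lesion (according to RECIST 1.1 criteria". Item 6 admits patients whose last intervention, radiotherapy or ablation ended more than 4 weeks earlier.

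**Response criteria.** Sections 2.1 and 7.1 make ORR primary, with RECIST v1.1 as the leading standard. Appendix II, 4.1 states: "In clinical protocols where objective response is the primary treatment endpoint, only patients with measurable lesions at baseline are eligible for inclusion". Appendix III, 4.1 repeats this for mRECIST. Appendix II, 4.3.1 defines PR as "A decrease of at least 30% in the sum of the diameters of all target lesions, relative to the baseline total diameter". For patients with non-target lesions only, Appendix II, Table 2 has the intermediate row "Non-CR or non-disease progression | Non | Non-CR or Non-Disease Progression"; its other outcomes are CR, not assessable and progression.

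**Locally treated lesions.** Appendix II, 3.1.3 says: "Tumor lesions located in previously irradiated areas or those subjected to other local treatments are generally not considered measurable", with an exception for lesions shown to be still active. Appendix III, 3.1.3 makes the exception for clear progression. Both ask the study protocol to lay down the conditions.

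**Denominator.** Section 7.4.4 defines ORR as a proportion of subjects and treats an unknown or missing best response as non-response. Section 10.1 builds the FAS from subjects treated at least once, less removed cases. Neither mentions measurable disease.

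**Baseline scan.** The Protocol Summary says "examinations conducted within 4 weeks prior to screening at the same institution are acceptable". Section 6.1 says "if they were performed within 4 weeks before enrollment and at this research center, they do not need to be repeated". Appendix III, 3.2.1 says baseline lesion measurements "must be completed within 28 days (4 weeks) prior to the start of treatment", and Appendix II, 3.2.1 also sets a four-week limit before treatment.

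**The concern.** The entry rule is looser than the response criteria that the primary endpoint depends on. If assessable is read to include non-measurable disease, a subject can be properly enrolled, be treated, and remain in the FAS with no route to PR. Section 4.4 would not take that subject out for breaching eligibility, because item 8 as written is met. The effect on ORR is downward. DCR is touched as well: Section 7.4.5 counts CR, PR and SD, and the non-CR/non-progression category is none of these, although the note under Table 2 describes it as better than SD.

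The scan windows are a second and separate matter. The baseline diameter sum is the reference for PR and can be the reference for progression. Sites following the Protocol Summary and sites following Section 6.1 would apply different limits to its age. If the tumor grows between the scan and the first dose, the recorded baseline is too small.

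**Working it through.** **1. Is there a figure to reproduce?** No. Section 3.2 fixes 30 subjects with no null rate, target rate, alpha or power, and Section 10.3.1 plans only an estimate with a 95% Clopper-Pearson interval. The point therefore bears on the estimate, not on a power claim.

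**2. Can a subject without target lesions be a responder?** PR needs a 30% fall in a sum of target-lesion diameters. With no target lesion that sum does not exist, and Table 2 offers no PR and no SD. CR remains possible.

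**3. Can such a subject enter?** Item 8 does not say measurable. Appendix II divides lesions into measurable and non-measurable (3.1) and gives response rules for both kinds of patient, so assessable by RECIST can be read to cover either. Item 6 supplies a plausible route: a patient whose only lesions were ablated or irradiated, with no rule in the protocol body on when those count as measurable.

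**4. Effect on expected ORR.** Let p be the response rate in subjects with measurable disease, k the number without it, and c the CR rate in those k.

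Expected FAS ORR = [p(30 − k) + ck] / 30, so each such subject costs (p − c)/30. With c = 0, the cost is p/30:

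- p = 30%: 0.30/30 = 1.0 point
- p = 50%: 0.50/30 = 1.7 points
- p = 63.9%: 0.639/30 = 2.1 points

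The 63.9% is the RECIST ORR of the lenvatinib, toripalimab and HAIC trial described in Section 1.5, used only as an illustration. The values of k below are assumptions; the protocol gives none.

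| p | k = 0 | k = 1 | k = 2 | k = 3 | k = 5 |
| --- | --- | --- | --- | --- | --- |
| 30% | 30.0% | 29.0% | 28.0% | 27.0% | 25.0% |
| 50% | 50.0% | 48.3% | 46.7% | 45.0% | 41.7% |
| 63.9% | 63.9% | 61.8% | 59.6% | 57.5% | 53.3% |

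For scale, 15/30 has a Clopper-Pearson interval of 31.3% to 68.7%.

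**5. Oldest permitted baseline scan.** Inputs: 4 weeks = 28 days; screening of up to 14 days (Section 6.1); first donafenib dose within 24 hours of enrollment (Section 6.2).

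| Source | Counted back from | Oldest at enrollment | Oldest at first dose |
| --- | --- | --- | --- |
| Protocol Summary | screening | 28 + 14 = 42 days | 42 + 1 = 43 days |
| Section 6.1 | enrollment | 28 days | 28 + 1 = 29 days |
| Appendices II and III, 3.2.1 | start of treatment | not stated | 28 days |

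Section 6.1 and the appendices agree to within a day. The Protocol Summary is the outlier.

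**The case against.** The strongest defense is that item 8 is tied to RECIST 1.1, and the appended criteria already restrict entry to measurable disease when response is primary. Assessable may simply be a translation of measurable, and the appendix itself is described as an internal translation. Diffuse tumors are excluded. A previously treated lesion does not make a patient non-measurable, since one untreated or recurrent lesion is enough. Appendix II already gives a default for treated lesions. Any bias lowers ORR, which is the cautious direction in a descriptive single-arm study with no decision threshold.

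Much of this stands as a limit on size. It does not remove the conflict: the operative eligibility text and the appendix use different words, the appendix has response rules for patients without target lesions, and the rule on treated lesions that both appendices ask the protocol to supply is not in its body.

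On scan age, a fair objector would say that Section 6.1 is the operative text and is within a day of the appendices. That is right. A reader might infer from the Protocol Summary that the plan as a whole accepts scans 42 days old at enrollment; that holds only if the Summary is followed and all 14 screening days are used. A reader might also infer that an old scan rules out a PR, or that growth before treatment would be scored as progression. Neither follows. A patient with target lesions can still reach PR from an old baseline, and the documents give no growth rate from which to show that the progression threshold would be crossed.

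**Conclusion.** The eligibility conflict is real and worth correcting. Item 8 can admit subjects who may be unable to score a PR and who would still count in the ORR denominator. The expected loss is p/30 per such subject, 1.0 to 2.1 points for p between 30% and 63.9%, assuming none of them reaches CR; any CRs among them make the loss smaller. The number affected is unknown and may be zero, so it should not be said that some subjects certainly cannot respond. Nor should the loss be put at 1/30, or 3.3 points, per subject: that is the fall in the highest attainable PR rate, not in expected ORR.

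Read literally, the non-CR/non-progression category also falls outside DCR.

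The scan windows are an internal contradiction to reconcile. They may bias the baseline diameter sum, by an amount that the documents do not allow one to size.

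**What to change.** 1. In the Protocol Summary and Section 4.1, change item 8 to require *at least one measurable lesion per RECIST 1.1*.
2. Add to item 8 that a lesion previously treated by radiotherapy, ablation or another local procedure counts as measurable only if it has clearly progressed since that treatment. This supplies the condition that section 3.1.3 of both appendices asks the protocol to state.
3. Give the Protocol Summary and Section 6.1 one scan window: baseline CT/MRI no more than 28 days before the first donafenib dose.

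The cost is a few lines of wording, rare screen failures and an occasional repeat scan. The sample size and the planned ORR analysis do not change.
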